For each program/team participating in the study, the following information will be collected on the organisational level: team size in staff and full-time equivalent (FTE), team composition in terms of discipline, academic level, years of experience in working with PD and MBT/ST/GIT-PD, and therapy registrations, including those for MBT and ST. For each participant, the actual duration of treatment in days, minutes of treatment, and the number of therapy sessions are obtained from the electronic patient file upon treatment completion or dropout. Furthermore, to assess the general type of institutional context and support, we will use the program adherence scale of MBT as a blueprint for identifying optimal institutional conditions for *both* specialist treatments [57], as there is no ST-specific counterpart. Additionally, we will use the quality criteria for GIT-PD from the Dutch Centre of Expertise on Personality Disorders.

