### Sample size {19}

The required sample size was determined using a computer simulation. Twenty-one thousand datasets with varying sample sizes were simulated for an RCT design with seven repeated measurements on a continuous outcome variable, where both interventions exhibit equal improvement over time. The outcome measures were assumed to follow a multivariate normal distribution in both groups, with a repeated measures correlation of 0.50 and a decrease of *d* = 0.30 in both groups across the seven repeated measurements. Each of these datasets was analysed using a longitudinal multilevel model (see *Statistical methods for primary and secondary outcomes, including harms {27a}).* Subsequently, in each dataset, it was tested whether generalist treatment is non-inferior to specialist treatment by examining whether the lower limit of the two-sided 95% confidence interval of the difference between treatments in improvement over time is greater than the non-inferiority limit of *d* = 0.25. It was found that with this design, 316 participants are necessary (158 per group) to test non-inferiority with a power of 0.80 and α = 0.025. To account for attrition, which we estimate at 11.7% for the primary endpoint (T4) based on a similar study [19], the complete sample needs to consist of (316/0.883 = 357.87) 358 participants. This comes down to 179 participants per treatment condition.

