#### Method of sequence generation {21b}

Participants will be randomised to either the experimental or comparator condition with a 1:1 allocation. Block randomisation, with varying block sizes of 4, 6, and 8 subjects, is stratified per participating mental healthcare institution.

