### Statistical methods

#### Statistical methods for primary and secondary outcomes including harms {27a}

*Non-inferiority.* The primary research question is answered through longitudinal multilevel modelling of the short-term difference (T4; 18 months) between generalist (GIT-PD) and specialist treatment (MBT/ST) in improvement of personality functioning, following the intention-to-treat principle. Two separate multilevel mixed-effects models are used for the two primary outcomes, meaning both the STiP-5.1 at two time points and the LPFS-BF 2.0 at five time points. The model levels refer to the repeated measurements (level 1) of each individual (level 2) nested within treatment sites (level 3). Both models will be adjusted for the respective baseline outcome value, while random intercepts and slopes are modelled to account for the heterogeneous individual change trajectories over time. Furthermore, random intercepts and slopes are modelled on the treatment site level to account for heterogeneous change trajectories across sites. No further covariates will be added. Two-tailed significance levels are set at *α* = 0.05, while effect estimates are reported with corresponding 95% two-sided confidence intervals. If the required sample size is not achieved due to problems with enrolment and inclusion, all non-inferiority analyses are converted to a one-sided confidence interval approach in order to retain sufficient statistical power. In case of convergence issues, the model’s complexity will be reduced by 1) not modelling the random slope but only the random intercept at the third level of treatment site, 2) replacing treatment site with institution with regards to the third level along with the respective random intercepts and slopes, or 3) omitting the third level in the analysis altogether if necessary. Trial-level non-inferiority will be assessed using a fixed-sequence testing procedure [117], prioritising the clinician-rated LPF (STiP-5.1) due to its blinded assessment and superior capability of measuring latent PD severity [58, 59]. If non-inferiority is demonstrated on the STiP-5.1, the self-reported LPFS-BF 2.0 will be tested subsequently to provide additional supportive evidence, given its high sensitivity to change [60]. If non-inferiority is not demonstrated on the STiP-5.1, the LPFS-BF 2.0 will not be formally tested as a primary outcome, and non-inferiority cannot be concluded at the trial level. This hierarchical approach preserves statistical power while controlling the family-wise error rate across multiple endpoints and prioritising blinded assessment to minimise potential bias.

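### The primary model has no term for the arm-specific programmes that deliver care, so clustering by programme would push towards false non-inferiority; separately, the last convergence fallback drops the randomisation stratum

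*Protocol article*

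**What the plan says.** All references are to the protocol article.

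- **Randomisation** (Method of sequence generation {21b}): it "is stratified per participating mental healthcare institution". There are five institutions with 11 sites (Trial setting {13}).
- **Primary model** (Statistical methods {27a}): measurements within individuals within treatment sites, with random intercepts and slopes for individuals and for sites, adjusted for the baseline value of the outcome. Then: "No further covariates will be added".
- **Convergence fallbacks** (same section): first drop the site slope, then use institution in place of site with its own intercepts and slopes, and finally "omitting the third level in the analysis altogether if necessary".
- **Both arms at each site** (Eligibility criteria for intervention deliverers {14b}): a site takes part only if it offers GIT-PD and at least one of MBT and ST.
- **Delivery** (Intervention description {15a}): the arms are defined partly by different team make-up, training and supervision. GIT-PD includes group modules, and ST is described in individual and group formats. Under {15c}: "For each program/team participating in the study, the following information will be collected on the organisational level".
- **Sample size** ({19}): "316 participants are necessary (158 per group) to test non-inferiority with a power of 0.80 and α = 0.025". The description of the simulation mentions no clustering by site, team or group.

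**The concern.** A site effect common to both arms cancels, or nearly so, from the treatment comparison. It therefore cannot represent the fact that patients in one arm at one site share a team, its supervision and often a therapy group, while patients in the other arm at that site share a different one. If that sharing affects outcomes, the model counts programme-level variation as independent patient-level variation. The standard error of the treatment difference is then too small. In a non-inferiority trial, an interval that is too short puts the lower limit above the margin too often, so the error runs in the direction the trial can least afford.

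The fallback sequence raises a second, smaller matter. Its last step leaves no centre term at all, although allocation was balanced within institution.

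**Working it through.** **1. The plan's own figure.** Inputs from Sample size {19}: margin 0.25, one-sided 0.025, power 0.80, correlation 0.50, seven measurements, no true difference ("both interventions exhibit equal improvement over time"). For a linear change over seven equally spaced measurements with constant correlation, the variance of the total change is 6² × (1 − 0.5) / 28 = 0.643. Then n per group = 2 × 0.643 × (1.960 + 0.842)² / 0.25² ≈ 162, or 324 in total against the stated 316. Power at 158 per group is 0.791. Attrition: 316 / 0.883 = 357.87, so 358. The stated size is thus reproduced to within 2.5%, with no allowance for clustering.

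**2. Cluster size (assumption).** One programme per arm per site gives 11 × 2 = 22 units, so m = 316 / 22 ≈ 14.4 evaluable patients each. The ICC is assumed, because the article gives none.

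**3. Error if clustering is ignored, and power if it is modelled.**

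- Design effect: DE = 1 + (m − 1) × ICC
- One-sided error if ignored: Φ(−1.960 / √DE)
- Power at 316 if modelled: Φ(2.802 / √DE − 1.960)

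| ICC | DE | Error if ignored | Power if modelled |
|---|---|---|---|
| 0.01 | 1.13 | 3.3% | 0.75 |
| 0.02 | 1.27 | 4.1% | 0.70 |
| 0.05 | 1.67 | 6.5% | 0.58 |

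**4. Second formula, baseline-adjusted 18-month comparison.** The residual variance is 1 − 0.50² = 0.75.

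- True variance of the difference: 2 × 0.75/158 + 2 × ICC/11
- Variance the model would report, with programme variation pooled into the residual: 2 × (0.75 + ICC)/158

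At ICC 0.02 these are 0.01313 and 0.00975, a standard-error ratio of 1.16 and an error of Φ(−1.960/1.16) ≈ 4.6%. At ICC 0.01 and 0.05 the error is 3.5% and 7.4%. Leaving the programme variance out of the reported residual gives 3.6%, 4.8% and 8.1%.

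**5. Simulation.** 3,000 trials per scenario, 316 patients, 11 sites in five institutions, blocks of 4, 6 and 8 within institution, one outcome value per patient, and the true difference set at the margin. Monte Carlo standard error is about 0.3 to 0.6 percentage points.

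| Source of clustering (assumed ICC) | Level 3 = site | Level 3 = institution | No level 3 |
|---|---|---|---|
| Shared site 0.05 | 2.7% | 2.5% | 2.5% |
| Shared site 0.10 | 2.5% | 2.3% | 2.2% |
| Institution 0.05 plus site 0.03 | 2.4% | 2.4% | 2.2% |
| Arm-specific programme 0.02 | 5.3% | 5.3% | 5.3% |
| Arm-specific programme 0.05 | 6.9% | 6.9% | 6.8% |
| Arm-specific programme 0.10 | 11.4% | 11.2% | 11.1% |

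At programme ICC 0.05 the site model reports a mean standard error of 0.088 against an actual spread of 0.117. A random site-by-arm intercept with t on 20 degrees of freedom brings the last three rows to 2.7%, 2.2% and 3.1%.

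**6. Effect of the last fallback.** With institution and site effects both present, dropping level 3 gives a mean standard error of 0.0886 against an actual 0.0853, about 4% too wide (0.0886 / 0.0853 = 1.04).

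**The case against.** **A reader might infer that using site instead of the stratum makes the main model wrong or weak.** It does not. Sites nest within institutions, so a site effect already absorbs differences between institutions, and the second fallback uses the stratum itself. Power gains can be computed for institution adjustment. With residual variance 0.75 and institution explaining 5-10% of the variance, power at 158 per group goes from 73% to 76-79%. But that compares against a model with no centre term, which is the last fallback and not the planned analysis.

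**A reader might also infer that the last fallback causes false non-inferiority.** The simulation rules this out. Removing a level shared by both arms is neutral to slightly conservative, and under programme clustering all three specifications fail alike. The gap is already in the full model.

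**The size rests on an ICC that the documents do not give.** This stands. The 22 units are also an assumption: {15a} allows a site several specialist programmes or formats, and the article does not say whether any staff work in both arms. The 8.1% in step 4 should not be used, since it lies above every other check at ICC 0.05.

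**The last fallback is only a last resort.** True, but it may not be remote. The STiP-5.1 model has two time points, where a person-level intercept and slope plus residual need four parameters for three covariance elements. The fallbacks simplify only level 3, so they could run to the end without curing this.

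Deferral to a separate analysis plan does not answer the point. The administrative table says the analysis plan is available in this publication, and {27a} closes the list of terms.

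**Conclusion.** The point holds in two parts of unequal weight.

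The main part is that no step of the primary analysis has an arm-specific cluster term, although delivery is by arm-specific programmes and partly in groups. If outcomes cluster that way, one-sided error is about 3.3-3.6%, 4-5% and 6.5-7.5% at ICC 0.01, 0.02 and 0.05, against 2.5%; the simulated 5.3% at 0.02 is just above that band, within Monte Carlo error. These figures assume 22 equal site-by-arm units and 316 evaluable patients. At an ICC near zero nothing is wrong, so this is a conditional risk and not a demonstrated error. It should be dealt with because its direction favours the trial's hoped-for conclusion.

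The minor part is that the last fallback discards the randomisation stratum. This costs a little precision and does not threaten the error rate.

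**What to change.** 1. **Stratum.** Replace the last fallback by a model with institution (five levels) as a fixed effect, and keep that effect at every fallback step. This is a wording change at no practical cost.
2. **Programme clustering.** Add a random site-by-arm effect on the 18-month contrast, with a small-sample degrees-of-freedom correction, at least as a pre-specified sensitivity analysis of the primary non-inferiority conclusion. Put it beside the shared site effect, not in its place: in the simulation, a site-by-arm term alone was too conservative when shared site variation was present (1.0% error at site and programme ICC both 0.05). If it does not converge, use cluster-robust inference by site-by-arm with a small-sample correction. Simply dropping the term and keeping institution would restore the original risk.
3. **Sample size.** State an assumed ICC and its effect on the 80% power: about 0.75, 0.70 and 0.58 at 316 evaluable for ICC 0.01, 0.02 and 0.05, before the further loss from a t reference distribution.

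**Cost.** Site and arm are known for every participant, so no new data are needed. Site-by-arm remains a proxy where a site runs several specialist programmes; the article does not state that each participant's team or group is recorded. The interval will be wider and the stated power lower if clustering exists. There is some cost even without it: at ICC 0 the mean standard error in the simulation rose from 0.0891 with the site model to 0.0945 with site-by-arm. Enrolment runs to the end of 2026 and data collection to December 2029 (Trial status), so the change can be made before the data are analysed.

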#### Predictors

The aforementioned secondary instruments assessed at baseline will also serve as candidate predictors in the PAI analysis. These candidate predictors have been selected based on previously identified predictors in comparable analyses [45, 82], as well as alignment with variables examined in ongoing or upcoming trials on optimal treatment selection for personality disorders [83–86]. Moreover, their inclusion allows for replication and verification of related findings, enhancing the robustness of predictor research surrounding PD.

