*Cost-effectiveness.* To assess the cost-effectiveness of treatments, we will conduct a comprehensive economic evaluation consisting of a cost-effectiveness analysis (CEA) and a cost-utility analysis (CUA). The analyses will be conducted and reported following [118], the CHEERS 2022 statement [119] and the ISPOR good research practices task force report on cost-effectiveness analysis alongside clinical trials II [120]. To evaluate the cost-effectiveness, improvement in LPF (as measured with the LPFS-BF 2.0 and STiP-5.1) is set off against costs incurred from the societal perspective. Treatment costs within the context of the participating mental health treatment centres are measured using patient file data (e.g. treatment minutes and type of therapist). Costs outside of the participating treatment centres are assessed with the TiC-P questionnaire. The TiC-P has a recall period of 3 months, which will be linearly extrapolated to complement the full intervals between time points. All cost estimates will be based on reference pricing as defined by Hakkaart-Van Roijen et al. [121].

For the CUA, health utilities are calculated using the Dutch tariff for the EQ-5D-5 L [122]. These utility scores will be used to calculate quality-adjusted life years (QALYs). QALYs gained between baseline measurements and the primary endpoint at 18 months after the start of treatment are the outcome variable for the CUA. This outcome variable is defined as the number of life years gained adjusted for quality of life. By projecting QALYs gained per condition as an operationalisation of utility, the cost-utility of the assigned intervention will be determined. In sum, we aim to execute the CEA and CUA from the societal perspective based on intention-to-treat analyses with an estimated time-horizon of 18 months after T0 for the economic evaluation on the primary endpoint.

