For both the CEA and CUA, the incremental costs (electronic patient file data and TiC-P) and the incremental effects (change in LPF as measured with the LPFS-BF-2.0 and STiP-5.1 for the CEA; QALYs as measured with the EQ-5D-5 L for the CUA) will be used to calculate incremental cost-effectiveness ratios (ICER). The uncertainty and robustness of the ICER will be analysed using bootstrapping. Next, the bootstrapped ICER will be plotted on cost-effectiveness planes where the horizontal axis displays the difference in effectiveness and the vertical axis displays the difference in costs. Further, the ICER will be used to examine willingness-to-pay (WTP) levels and then will be plotted in cost-effectiveness acceptability curves, displaying the cost-effectiveness of the experimental condition compared to the active control condition. Hence, WTP analysis will be conducted to determine the incremental costs per incremental unit of effect (QALYs or change in LPF) gained compared to WTP thresholds. A fitting discount rate will be applied for outcomes and future costs in accordance with NICE guidelines [123] and Drummond et al. [118]. Uncertainty in results will be assessed using both bootstrapping and sensitivity analyses. Variability and heterogeneity analyses will be conducted. Potential subgroups based on patient characteristics will be part of exploratory analyses.

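### No baseline adjustment is specified for the incremental cost, although a pre-randomisation TiC-P is very probably available; adjusting for it would be a minor, nearly free gain in precision

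*Protocol article*

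**What the plan says.** All references are to the protocol article.

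- **Cost difference.** Section {27a}, Cost-effectiveness, names two sources: "the incremental costs (electronic patient file data and TiC-P) and the incremental effects" are combined into ICERs. On uncertainty it says: "The uncertainty and robustness of the ICER will be analysed using bootstrapping". It names no estimator or covariate for the cost difference.
- **What each source covers.** For care inside the centres: "Treatment costs within the context of the participating mental health treatment centres are measured using patient file data". For the rest: "Costs outside of the participating treatment centres are assessed with the TiC-P questionnaire". On timing: "The TiC-P has a recall period of 3 months, which will be linearly extrapolated to complement the full intervals between time points".
- **Baseline TiC-P.** The TiC-P is described under Secondary outcome measures. The Predictors section then says: "The aforementioned secondary instruments assessed at baseline will also serve as candidate predictors in the PAI analysis". Implementation {23} places randomisation after the baseline measurements are complete.
- **Clinical outcomes, for contrast.** For the two primary outcomes, section {27a} says: "Both models will be adjusted for the respective baseline outcome value". The same holds for the seven secondary clinical parameters listed there. Costs are not on that list.
- **Where the plan is held.** Item {5} of the administrative table says that the statistical analysis plan is in this publication, and in part in the ethics-approved protocol. Section {27d} plans no further analyses.

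**The concern.** A person's care use and productivity loss tend to persist, so cost in the months before randomisation is a natural covariate for later cost. Randomisation is stratified by institution only, so nothing in the design balances prior cost within institutions. The sample size was set for the clinical non-inferiority test, not for costs.

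The third secondary objective asks whether generalist treatment is more cost-effective, and that answer rests on the cost difference. Without adjustment, any chance difference in prior cost passes into the cost-effectiveness plane and the acceptability curve, and the interval is wider than it needs to be. An unstated estimator also leaves the choice between an adjusted and an unadjusted cost difference open until results are known.

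**Working it through.** **Inputs from the article.** 316 participants before attrition, 11.7% attrition, 1:1 allocation (Sample size {19}). The article gives no cost SD, cost difference or cost correlation.

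**The article's own figure.** 316 / (1 − 0.117) = 357.87, so 358, or 179 per arm; this reproduces. As a rough check on the 316: for linear change over seven equally spaced measures with correlation 0.50, the variance is 36 × (1 − 0.50) / 28 = 0.643. With margin 0.25, one-sided alpha 0.025 and power 0.80, this gives 162 per arm against the stated 158, within 3%.

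**Unadjusted cost difference.** In units of the cost SD, the standard error is √(2/179) = 0.106 and the 95% half-width is 1.96 × 0.1057 = 0.207.

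**Adjusted cost difference.** Let r be the correlation between the T0b TiC-P cost and total follow-up cost. Adjustment multiplies the standard error by √(1 − r²). The values of r are assumptions.

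| r (assumed) | width ratio √(1 − r²) | narrowing | 95% half-width (SD) |
|---|---|---|---|
| 0.1 | 0.995 | 0.5% | 0.206 |
| 0.2 | 0.980 | 2.0% | 0.203 |
| 0.3 | 0.954 | 4.6% | 0.198 |
| 0.4 | 0.917 | 8.3% | 0.190 |
| 0.5 | 0.866 | 13.4% | 0.179 |
| 0.6 | 0.800 | 20.0% | 0.166 |

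**Chance imbalance.** The difference between arms in mean baseline cost also has a standard error of 0.106 SD. An imbalance of that size moves the unadjusted follow-up difference by r × 0.106 SD: 0.011 SD at r = 0.1, 0.042 at r = 0.4 and 0.063 at r = 0.6.

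**Why r may be low.** The TiC-P covers only part of total cost. Suppose out-of-centre cost makes up a share s of total cost variance and correlates c with its own baseline, while in-centre cost is unrelated to either. Then r² = s × c².

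- s = 0.5 to 0.9 and c = 0.3 to 0.6 give r² = 0.045 to 0.324, and a standard error 2.3% to 17.8% smaller.
- s = 0.2 to 0.5 and c = 0.1 to 0.3 give r² = 0.002 to 0.045, and a standard error 0.1% to 2.3% smaller.

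**Skewed costs.** In a simulation of 4,000 trials per setting, with log-normal costs, 179 per arm and the correlation set on the log scale, the ratio of adjusted to unadjusted standard error was 0.987, 0.953 and 0.859 for correlations of 0.2, 0.4 and 0.6. These are reductions of 1.3%, 4.7% and 14.1%, against 2.0%, 8.3% and 20.0% in the table. No arm difference was simulated, and both estimators averaged close to zero.

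**The case against.** The strongest objection is that the article never says costs are compared raw. It names data sources and bootstrapping, and it is equally silent on the estimator for the incremental effects. An article may condense its economic methods, and this one points to published economic-evaluation guidance. A reader might infer a deliberate choice of raw costs; the text does not support that. The silence still counts to some extent, because item {5} places the analysis plan in this publication and {27d} plans nothing further. The supportable statement is that no adjustment is specified.

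Other limits also stand:

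- A reader might infer that each participant's full prior cost is recorded. The TiC-P covers only costs outside the centres over three months. In-centre treatment cost comes from patient files, and the Discussion calls dosage and duration defining differences between the arms. The parallel with clinical outcomes adjusted for their own baseline is therefore loose.
- That the TiC-P is given at T0b is inferred. Table 1 is not shown, and the Predictors sentence could mean only those secondary instruments that happen to be given at baseline. Nor does the article say which TiC-P forms enter the cost total, so one cannot assert that the baseline form has no other role in the cost analysis.
- Participant timeline {18} allows for waits of ten weeks, or six months and more, before treatment starts. Follow-up runs from the start of treatment, so an early baseline window may predict later cost less well.
- A reader might infer bias. There is none: under randomisation the unadjusted difference is unbiased, and a valid interval for it already reflects chance imbalance.

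**Conclusion.** The point holds as a minor, nearly free improvement to a secondary economic analysis. As written, the plan specifies no baseline adjustment for the incremental cost. The resulting estimate is unbiased, but it is open to chance imbalance in prior care use and productivity loss and is less precise than the data allow.

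The interval would narrow by about 0.5% to 8% for r between 0.1 and 0.4, and by up to 20% at r = 0.6. Skewed costs and long waits push the gain down, and it could be negligible. A reader might infer from the top of the range that a large effective sample is being lost: at r = 0.6, 358 / (1 − 0.36) = 559 participants. The article gives no basis for assuming a correlation that high.

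The conclusion assumes that the TiC-P is completed at T0b before randomisation, and that baseline cost predicts total follow-up cost to some degree. It does not touch the primary non-inferiority analysis or the estimation of personality functioning or QALYs.

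**What to change.** In section {27a}, Cost-effectiveness, state that the incremental cost is estimated by regression of total cost on arm with the T0b TiC-P cost as covariate. Specify the T0b value: where there is a waiting list, a T0p re-measurement follows randomisation and should not be used. Refit the regression within each bootstrap sample, jointly with the effect, so that the plane and acceptability curve use the adjusted cost difference. Continue to report unadjusted mean costs by arm.

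The cost is a sentence or two in the economic analysis, with no new data if the TiC-P is indeed given at T0b; confirm this against the assessment schedule first. Two practical matters need a line each: the handling of a missing baseline form, which should be uncommon because electronic entry enforces item completion, and a check on very high baseline costs, which can have strong leverage in the regression.

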### Outcomes {16}

The first primary outcome is the mean difference in change from baseline to end of treatment (T4) in clinician-rated personality functioning between the generalist (GIT-PD) and specialist treatment (MBT/ST) conditions, as assessed with the clinical STiP-5.1 interview. Furthermore, the second primary outcome refers to the mean difference in change from baseline to end of treatment (T4) in self-reported personality functioning between the generalist (GIT-PD) and specialist treatment (MBT/ST) conditions, based on the Level of Personality Functioning Scale – Brief Form 2.0 (LPFS-BF 2.0) questionnaire. Inclusion of the STiP-5.1 interview measure allows for blinded, clinician-rated outcome assessment, which reduces potential bias [58]. Moreover, interview measures capture a larger proportion of the variance of a latent general PD severity than self-reported questionnaires [59]. However, the use of the STiP-5.1 in psychotherapy research is novel, leading to little knowledge on the measure’s sensitivity to change [53]. Concurrently, the self-reported LPFS-BF 2.0 questionnaire has demonstrated high sensitivity to change, while its use is more established in international research [60, 61]. Therefore, the STiP-5.1 interview is given priority regarding the primary outcome, but supplemented with the self-reported LPFS-BF 2.0 questionnaire.

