
To answer the secondary research questions regarding long-term (T6; 30 months) non-inferiority of generalist (GIT-PD) versus specialist treatment (MBT/ST) in improving personality functioning, an identical intention-to-treat longitudinal multilevel model will be fit as for the primary outcome, while including all available repeated measures. This ultimately results in the inclusion of three and seven repeated measures for the STiP-5.1 and LPFS-BF 2.0, respectively. Likewise, to assess the short-term (T4; 18 months), as well as the long-term (T6; 30 months) non-inferiority of generalist (GIT-PD) versus specialist treatment (MBT/ST) in improving symptom severity and psychosocial functioning, the same intention-to-treat longitudinal multilevel model will be applied for each of the secondary study parameters (SIPP-SF, SCID-5-PQ, BSI, C-SSRS, WHODAS 2.0, EQ-5D-5 L, Q-LES-Q-SF). Likewise, for the short-term outcome, the five repeated measures (level 1) of each individual (level 2) are nested within treatment sites (level 3). Models are adjusted for the respective outcome’s baseline value, random intercepts, and slopes are modelled at the second and third level to account for heterogeneous individual and treatment site change trajectories over time, and two-tailed significance levels are set at *α* = 0.05, while effect estimates are reported with corresponding 95% two-sided confidence intervals. The non-inferiority margin is set at *d* = − 0.25. On top of that, all AEs and SAEs are descriptively reported for both treatment arms.

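### The cost-utility analysis accumulates QALYs from baseline with no adjustment for baseline EQ-5D-5L utility, and the cost-effectiveness analysis does not tie its LPF effect to the baseline-adjusted clinical estimate

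*Protocol article*

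**What the plan says.** All places are in the protocol article.

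- **CUA outcome** (Statistical methods {27a}, Cost-effectiveness): "QALYs gained between baseline measurements and the primary endpoint at 18 months after the start of treatment are the outcome variable for the CUA". QALYs are then compared by condition.
- **ICER** (same section): incremental costs are set against "the incremental effects (change in LPF as measured with the LPFS-BF-2.0 and STiP-5.1 for the CEA; QALYs as measured with the" EQ-5D-5L. The ICER is bootstrapped, plotted on the cost-effectiveness plane and turned into acceptability curves. Neither a baseline covariate nor institution is mentioned.
- **Primary LPF models** (same section, Non-inferiority): "Both models will be adjusted for the respective baseline outcome value".
- **Secondary models**, which include the EQ-5D-5L: "Models are adjusted for the respective outcome’s baseline value".
- **Method of sequence generation {21b}**: randomisation is stratified by institution.
- **Administrative table, item {5}**: the statistical analysis plan is said to be available in this publication, and in part in the ethics-approved protocol.

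**The concern.** A QALY accumulated from baseline is an area under the utility curve, and the baseline value is its first point. An arm that happens to start with higher utility therefore gains QALYs before treatment can act, and continues to gain them because later utilities correlate with the first. The secondary EQ-5D-5L model does not repair this: it analyses the repeated scores and not the accumulated QALY.

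For the CEA the issue is consistency. The same two instruments, at the same 18-month endpoint, are adjusted for baseline in the primary analysis, while the economic section refers only to change in LPF.

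Cost-effectiveness is one of the trial's three main questions. The sample-size simulation assumes equal improvement in both arms, so the effect difference in the ICER is expected to lie near zero. There, avoidable noise matters most: it widens the cloud on the plane, flattens the acceptability curve, and can put the point estimate on a different side of zero from an adjusted estimate on the same data.

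**Working it through.** **Inputs.** Correlation 0.50 (Sample size {19}: "with a repeated measures correlation of 0.50 and a decrease of" 0.30 SD); 158 analysed per arm before attrition (same section); visits at 0, 3, 6, 12 and 18 months (Participant timeline {18}). The text on the secondary models counts five repeated measures to T4, which fits this schedule, but Table 1 could not be read, so EQ-5D-5L at all five visits is an assumption. So are compound symmetry and the use of 0.50 for utilities, since the plan states that figure for its simulated outcome. The range 0.3 to 0.7 is shown. Site clustering is ignored.

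**The plan's own figure.** The economic section gives none. The 158 per arm is roughly reproduced by treating the contrast as fitted linear change over seven equally spaced measures:
- variance = 36 × 0.5 / 28 = 0.643
- n = 2 × (1.960 + 0.842)² × 0.643 / 0.25² ≈ 162 per arm; power at 158 is 0.79
- attrition: 316 / 0.883 = 357.9, so 358, as stated

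**QALY difference (utility SD = 1).** Trapezoid weights in years are w = 0.125, 0.25, 0.375, 0.5, 0.25 (sum 1.5; sum of squares 0.53125).
- Var(QALY) = (1 − r) × 0.53125 + r × 1.5²
- Cov(QALY, baseline) = 0.125 × (1 − r) + 1.5 × r
- Adjusted variance = Var − Cov²

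| r | Var | Cov | Adjusted var | SE ratio |
|---|---|---|---|---|
| 0.3 | 1.047 | 0.538 | 0.758 | 0.85 |
| 0.5 | 1.391 | 0.813 | 0.730 | 0.72 |
| 0.7 | 1.734 | 1.088 | 0.552 | 0.56 |

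At r = 0.5 the QALY–baseline correlation is 0.8125 / √1.391 = 0.69. With 158 per arm, a one-standard-error baseline imbalance is √(2/158) = 0.113 SD. It moves the unadjusted QALY difference by 0.8125 × 0.1125 = 0.091 SD-years, against an unadjusted SE of √1.391 × 0.1125 = 0.133. With no true difference, the unadjusted and adjusted estimates differ in sign with probability arccos(0.725)/π = 24% (18% at r = 0.3, 31% at r = 0.7).

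If QALYs gained were instead read as the area above each person's baseline level, the variance at r = 0.5 would be 1.391 − 2 × 1.5 × 0.8125 + 2.25 = 1.203, and the SE ratio √(0.730/1.203) = 0.78. Adjustment helps on either reading.

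**LPF difference (SD = 1, 158 per arm, r = 0.5).**
- Change score: SE = √(2(1 − r) × 2/158) = 0.113
- Baseline-adjusted: SE = √((1 − r²) × 2/158) = 0.097
- Correlation of the two estimates: √0.75 = 0.866
- Opposite signs at no true difference: arccos(0.866)/π = 16.7% (20.2% at r = 0.3, 12.7% at r = 0.7)
- Opposite signs by bivariate-normal simulation at r = 0.5: 10.8% at d = 0.10, 1.1% at d = 0.25

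**The case against.** The article never says that the economic effects are unadjusted; that is inferred from silence. A journal article condenses a fuller document, and this one commits itself to outside standards: "The analyses will be conducted and reported following [118], the CHEERS 2022 statement [119] and the ISPOR good research practices task force report". It also announces more than the bootstrap: "Uncertainty in results will be assessed using both bootstrapping and sensitivity analyses". The word change settles nothing, because Outcomes {16} describes the primary endpoint the same way ("The first primary outcome is the mean difference in change from baseline to end of treatment (T4) in clinician-rated personality functioning") and that endpoint is analysed with baseline adjustment. Randomisation makes chance imbalance a matter of variance and not of bias. If the true difference is zero, the sign of the adjusted estimate is also a coin toss, and the plane and acceptability curve are there to show it. All costs use reference prices, so institution-specific unit prices cannot be a reason to adjust.

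Most of this stands. A reader might infer that the CEA takes a simple difference in change scores, that the ICER is biased, or that the economic result will contradict the primary one. The documents support none of these. The LPF part therefore shrinks to a consistency point. Only LPF, and not the EQ-5D-5L, is in the primary models. The power of a superiority test on these effects is irrelevant, because the economic section plans none.

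The objection does not remove the QALY point. The article says it carries the analysis plan, and it fixes the CUA outcome along with the tariff, the extrapolation of costs and the bootstrap. Followed as written, this leaves baseline utility inside the outcome and unadjusted. A cross-reference to the clinical models would settle the LPF effect but would not produce an adjusted QALY difference. The sensitivity analyses have no stated content, and bootstrapping an estimator does not remove an imbalance present in the sample.

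**Conclusion.** The point holds for the CUA, and for the CEA as a gap in consistency. The consequence is avoidable imprecision and exposure to chance imbalance in the ICER, not average bias. For QALYs, adjustment would bring the standard error to about 0.72 of its unadjusted value, with 0.56 to 0.85 over the correlations considered. This rests on the assumed correlation, compound symmetry and five utility visits. For LPF the gain is smaller, and it arises only if unadjusted change scores are in fact used. Sign conflict is then likely enough to matter near a zero difference and rare at the size of the non-inferiority margin. This is an inexpensive improvement worth making, not an error that invalidates the economic evaluation.

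**What to change.** In the Cost-effectiveness part of Statistical methods {27a}, state that:

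1. the incremental QALY is estimated by regression on arm, baseline EQ-5D-5L utility and the stratification factor, institution;
2. the incremental LPF effect is adjusted for baseline LPF, using the same baseline measurement as the primary models. That measurement should be named, since Participant timeline {18} allows both a baseline (T0b) and a pre-treatment (T0p) assessment;
3. this adjusted estimation is repeated in every bootstrap sample together with the costs, so that the plane and acceptability curve reflect it.

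A joint cost and effect model such as seemingly unrelated regression is one suitable option, not a requirement. A single-time-point regression for LPF need not equal the three-level longitudinal estimate exactly, so the text should say which is used in the ICER.

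The cost is a few sentences and a standard regression within a bootstrap that is already planned, with no new data or participants. Settling it before outcome data are analysed also prevents a later choice between estimators that may disagree.
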